### Research questions, goals, and hypotheses

1.3.

The main goal of the present study is to investigate the effectiveness of a PL intervention in different schools in the city and city state of Bremen, Germany. This study addresses the following primary research question: *Can an intervention with clear foundations in the integrated PL domains systematically promote PL among children 8–11 years of age?* Accordingly, we will test the main hypothesis (one-sided procedure) that children in the intervention condition develop significantly better over the interventional period in PL outcomes compared to children in the control condition.

In addition, the present study pursues two sub-goals on its way toward the primary goal: (a) to derive holistic, age-specific intervention components for 8–11 years old children with explicit manifestations in the PL concept, and (b) to implement the intervention in cooperation with primary schools in the city and city state of Bremen, Germany. In case of a successful implementation and evaluation (i.e., approval of the research question), the present study also reserves capacities for potentially preparing the dissemination of the intervention concept.

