### Sample size

2.6.

We performed sample size calculations with the software G*Power version 3.1 (94). For the uncontrolled *pilot study* adopting a pre-post character, we expect a minimum effect size of *d_z_* = 0.40 while considering the influence of general development effects. In this case, the minimum sample size to be acquired through one-sided, paired sample *t* tests (statistical power ≥ 80% and one-sided *p* < .05) will be *n* = 41. Assuming a conservative dropout rate of 25% (as usual for this target group, see (14, 95), an initial sample of *n* = 55 children will be recruited. Given an average number of approximately 20 pupils per class, we will include three to four classes for the pilot study.

For the subsequent main study in a control group design, we base a significant effect on time-group interactions of repeated multivariate analyses of variance (MANOVA). Aiming to control for general development effects through the involvement of a control arm, we set a smaller effect size of *d* = 0.30 (corresponding to *f* = 0.15) in this part of the study. Power calculations with an adjusted significance level (five PL outcomes:.05/5) of *p* ≤ .01 resulted in a required sample size of *n* = 134 children across the two study conditions (autoregressive pre-post correlation *r_t_* = 0.50, statistical power ≥ 80%). A total of nine to ten classes (dropout corrected *n* = 179 children) should initially participate in the main study.

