#### Quantitative analysis

2.7.2.

The *pilot study* using a non-controlled pre-post design will be analyzed with paired sample tests. In this case, the time (pretest vs. posttest) will be treated as the independent variable and the PL domains as the dependent variables. Depending on the support or rejection of normal distribution (based on Kolmogorov Smirnov test), we will compute paired sample *t* tests or Wilcoxon tests for the inferential statistical comparison.

Furthermore, the Transparent Reporting of Evaluation with Non-Randomized Designs (TREND) statement will serve as an overarching framework (99) to guide the design, evaluation, and reporting of the *main study*. We will use a variance analytical design with multivariate character to quantitatively examine the effectiveness of the intervention arm in comparison to the control arm (repeated MANOVA). Statistically, main attention will be paid to the time-group interaction in the repeated MANOVA (within-subjects factor: time; between-subjects factor: group condition). We will determine the magnitude of the intervention effect on the eta square (*η*^2^) coefficient by adhering to the interpretation guidelines as suggested by Cohen (100). Despite the nested structure of data (e.g., classes as clusters), multilevel analysis (i.e., linear mixed methods) cannot be realized owing to the low number of second-order units (*N* ≤ 10 schools). Even robust methods, like the Kenward-Roger correction, require a larger number of clusters for adequate calculations (101). To account for potential clustering at the class level, we will enter the class as covariate within the MANOVA. Missing data in the longitudinal data set will be imputed with the expectation maximization (EM) algorithm (102). Nevertheless, we will withdraw children from the analysis who did not attend (a) the first session with the baseline measurement and (b) at least eleven of the 14 sessions (<75%; i.e., exclusion of those who were missing more than three sessions of the PL intervention).

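### EM-imputed scores analysed as observed ignore imputation uncertainty: standard errors are too small if condition is in the EM model, and the effect is attenuated if it is not

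*Protocol article*

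**What the plan says.** Section 2.7.2 (Quantitative analysis) fixes the method: "Missing data in the longitudinal data set will be imputed with the expectation maximization (EM) algorithm". The same section names the target of inference: "main attention will be paid to the time-group interaction in the repeated MANOVA". It gives no number of completed data sets, no residual draw, no variance correction and no list of variables in the EM model.

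The next sentence limits who can be imputed. Children without the baseline session, and children who miss more than three of the 14 sessions, are taken out of the analysis.

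Section 2.6 (Sample size) sets the error level, "Power calculations with an adjusted significance level (five PL outcomes:.05/5) of *p* ≤ .01", and the pre-post correlation, "autoregressive pre-post correlation *r_t_* = 0.50, statistical power ≥ 80"%. Its dropout figure, "Assuming a conservative dropout rate of 25"%, belongs to the pilot. For the main study the same rate is only implied by the step from 134 to 179 children.

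**The concern.** EM imputation in its usual form replaces each missing score by its conditional mean given the observed data. Such values carry no residual scatter and no uncertainty about the fitted regression. A standard MANOVA on the completed file counts them as full observations.

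Two faults can follow, and the article does not say which version it will use. With condition in the EM model the group difference is estimated fairly but its standard error is too small. With condition left out, imputed children in both arms are pulled to a common expected change, and the group difference shrinks.

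The main study is meant to inform whether the intervention is scaled up. Its significance level was lowered to .01 to protect five outcomes, and the first fault would undo part of that protection.

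**Working it through.** **The plan's own figure.** Inputs from section 2.6: "we set a smaller effect size of *d* = 0.30 (corresponding to *f* = 0.15) in this part of the study", r = 0.50, alpha 0.01, two time points. For the within-between interaction, λ = f²·N·2/(1 − r) = 0.0225 × 134 × 2/0.5 = 12.06. On 1 and 132 degrees of freedom the power is 0.803, and 134 is the smallest even N that reaches 80%. Then 134/0.75 = 178.7, so 179. The figures reproduce, and 25% is the main-study dropout they imply.

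**Set-up.** With two time points, the time-by-group test for one domain is a comparison of change scores. Assume unit-variance normal scores, N = 179 (90 and 89), r = 0.5, a share m of post-tests missing at random, and no class effect. Without missing data the change variance is 2(1 − r) = 1, and the SE is √(1/90 + 1/89) = 0.1495.

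**Case A: condition in the EM model, or EM per arm.**
- Reported variance factor: observed changes have variance 2(1 − r) = 1 and imputed changes only (1 − r)² = 0.25. The average is (1 − m) + 0.25m. At m = 0.25 this is 0.8125, so the reported SE is 0.1495 × √0.8125 = 0.135.
- True variance factor: (1 − r)² + (1 − r²)/(1 − m). At m = 0.25 this is 0.25 + 0.75/0.75 = 1.25, so the true SE is 0.1495 × √1.25 = 0.167.
- Ratio: √(0.8125/1.25) = √0.65 = 0.806.
- Two-sided type I error: 2Φ(−2.576 × 0.806) = 3.8% at nominal 1%, and 2Φ(−1.960 × 0.806) = 11.4% at nominal 5%.

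Simulation under no effect (15,000 runs per scenario) agrees:

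| Post-tests imputed | SE ratio | Error at nominal 1% | Error at nominal 5% |
|---|---|---|---|
| 25% both arms | 0.81 | 3.9% | 11.4% |
| 15% both arms | 0.88 | 2.3% | 8.3% |
| 10% both arms | 0.92 | 1.8% | 7.2% |
| 5% both arms | 0.97 | 1.2% | 6.0% |
| 25% control, 5% intervention | 0.88 | 2.5% | 8.3% |

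The hypothesis is stated as directional ("we will test the main hypothesis (one-sided procedure"). The corresponding one-sided test at 1% rejects in 3.0% of null trials at 25% imputed. For r from 0.3 to 0.7 the two-sided rate at nominal 1% runs from 3.6% to 4.3%.

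In a five-outcome MANOVA (N = 180, assumed between-domain correlation 0.3, 8,000 runs, 25% imputed) the rates are 8.4% at nominal 1% and 21.0% at nominal 5%. Adding a class code as covariate leaves the first at 8.3%. A single imputation with a random residual does not cure the univariate test (3.1% at nominal 1%).

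**Case B: condition left out of the EM model.** The SE ratio is 1.00, and rejection under no effect is 1.1% at nominal 1% and 4.9% at nominal 5%. Only the observed share carries the group difference, so a true 0.30 becomes about 0.30 × (1 − 0.25) = 0.225. The simulation gives 0.226.

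**Remedy checked.** Multiple imputation with condition in the model (20 imputations, Rubin's rules, 25% missing, 4,000 runs) rejects in 0.9% and 4.5% of null trials. Its mean SE is 0.169 against a true 0.169.

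**The case against.** A reader might infer that the planned method inflates false positives whatever the EM model. The document does not support that. Inflation needs condition in the model or separate EM by arm, and the article states neither. A group-blind EM keeps type I error nominal, and its fault works against a positive finding.

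A reader might also infer that 179 children enter as if all were measured, with 25% of post-tests imputed in both arms. The 25% is written for the pilot. In the main study the inflation from 134 to 179 allows for children leaving the analysis. The post-test is session 14, so an intervention child who quits after session 10 misses four sessions and is excluded, not imputed. Controls have no intervention sessions, so the rule cannot remove them in the same way, and imputation may fall mainly on that arm. Hence 25% in both arms is an upper bound, and error near 2% at nominal 1% is more realistic in Case A.

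It is also fair to say that the article does not state that values are filled in only once, and that the imputation variables are a detail an analysis plan may settle. Where only some items or domains are missing, EM could draw on the child's other post-test data, and the loss would be smaller than shown here.

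What remains is that the article commits to imputing and then to a standard MANOVA. A single completed data set is the natural reading, and naming the EM variables would only decide which fault applies.

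**Conclusion.** The point holds in conditional form: the stated method ignores imputation uncertainty.

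- **Condition in the EM model:** standard errors are up to about 20% too small if 25% of post-tests are imputed, with type I error about 4% at nominal 1% and 11–12% at nominal 5%. Error at nominal 1% is about 2% if 10% are imputed (1.8%), or if 25% of controls and 5% of intervention children are (2.5%).
- **Condition left out:** type I error is nominal, and the effect is attenuated roughly by the imputed share.

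These sizes assume normal scores, loss of the whole post-test occasion, missingness at random, r near 0.5 and no class effect. The multivariate figures also rest on the assumed correlation of 0.3. The amount of harm depends on how many scores are actually imputed, and at 5% it is slight.

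**What to change.** Replace the EM sentence in section 2.7.2 with one of two options.

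1. **Multiple imputation**, with condition, baseline scores of all domains, age and sex in the imputation model, each completed data set analysed as planned and the results combined by Rubin's rules. Use either condition or fixed class indicators, not both: whole classes are assigned to a condition, so class determines condition.
2. **A likelihood-based repeated-measures analysis** of all observed pre- and post-test scores, with no imputation. The article's objection to multilevel models concerns the small number of clusters, not the pre-post covariance within a child.

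The cost is a change of wording, modest programming and wider intervals. No change to data collection is needed.

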**Figure 1 F1:**
[figure not shown]
Study design.

After the completion of the two pilot studies, we will follow up with the main study. The main study will more rigorously examine the effectiveness of the final PL intervention in a controlled design. In each school, an even number of classes of one grade level will participate in the study. Half of the classes will be assigned to the intervention condition, which will pass regular half-year education in primary school plus a weekly PL intervention. In contrast, the other half of the classes will be assigned to the control condition, which will undergo only regular half-year education in primary school without the additional PL intervention (see Figure 1). Randomization cannot be fully realized as pragmatic reasons co-influence the assignment to the different intervention arms (57). The main study, which also includes two measurement time points (e.g., pre and post), will take place between September 2023 and February 2024. In summary, the research design with two pilot cycles (51) accounts for potential pitfalls (e.g., revision of PL content) toward a sound examination of the effectiveness of the PL intervention. The final reporting of study will adhere to the recent physical literacy interventions reporting template suggesting a total of 14 items (58). The ethics committee of the University of Oldenburg, Germany, has approved the conduction of the study (sign Drs.EK/2022/057).

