#### Intervention structure, organization, and content

2.3.1.

To develop a holistic, age-specific intervention for 8–11 years old children theoretically based on the PL concept (goal a), we will deliver an intervention program comprising a total of 14 individual sessions. The duration of the sessions will be aligned with the logistic and temporal situation at the recruited schools and can range between 60 and 90 min. To facilitate the arrangement of the school schedules and promote comparability, the frequency of sessions held will be one time per week. Each session will be driven by the concept of PL and will be implemented after the regular classes, e.g., in times of afternoon care, or in some schools in the context of an individual spare time in between the regular school day. In contrast to theory-inspired interventions, theory-based interventions cultivate explicit links between theory and content (70, 71). In the context of this intervention, each session will contain explicit links to all PL domains (see Table 1) in accordance with the selected definition and framework of PL (47): the physical, the cognitive, the affective, and the social domain. All sessions will be realized via actual movement (PA behavior), which implicates that theoretical inputs without an immediate transfer into practice will be avoided across the sessions. In reference to studies which criticized the separation of the different domains in previous PL interventions or the emphasis on a specific domain (the physical domain foremost) (24, 72), our aim will be to consider the integrated nature of PL in every single session. Accordingly, we will not treat the PL domains as isolated blocks, instead addressed the domains in an integrative manner (73).

**Table 1 T1:** A detailed overview of the theory-based PL intervention content.

Session	Main focus	Main goal	Theory-content link			
			Physical domain	Cognitive domain	Psychological (affective) domain	Social domain
1	Evaluation: Pretest	Self-evaluation, enabling PL charting	Mixed rule-based games focusing object control	Content knowledge: Reasons for evaluation	Self-perception	Fairness, inclusion
2	Cooperative game forms	Strengthen group structure	Game arrangements promoting cooperation and anticipation	Strategy and planning; Participatory development and operation with cooperation strategies	Focusing success experiences with the whole group	Communication; respect; solve team challenges

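### Dropping children who miss more than three PL sessions can remove children from the intervention arm only, so selected attenders are compared with unselected controls, which is likely to favour the intervention

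*Protocol article*

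**What the plan says.** The main-study paragraph of section 2.7.2 names two grounds for withdrawing a child from the analysis. Ground (a) is not having attended "the first session with the baseline measurement". Ground (b) is attending fewer than eleven of the 14 sessions, which the text explains as the "exclusion of those who were missing more than three sessions of the PL intervention". The same paragraph plans EM imputation for missing longitudinal data but still removes these children.

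Section 2.1 describes the two conditions. Intervention classes are those "which will pass regular half-year education in primary school plus a weekly PL intervention"; control classes are those "which will undergo only regular half-year education in primary school without the additional PL intervention". Section 2.3.1 places the sessions mainly in extracurricular time: they "will be implemented after the regular classes, e.g., in times of afternoon care".

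Section 1.3 states a one-sided main hypothesis that "children in the intervention condition develop significantly better over the interventional period in PL outcomes compared to children in the control condition". It does not confine the claim to children who attend regularly. The abstract says that the results will decide whether the intervention is scaled up. The article gives no attendance rule for controls, and the limitations in section 3.2 do not mention the exclusion.

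**The concern.** Attendance at PL sessions arises after classes are assigned, and it exists in one arm only. Ground (a) can apply to any child in either arm and is not the difficulty. Ground (b) can remove only intervention children. Controls who would have attended poorly, had they been offered the programme, stay in.

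The analysed arms then differ by design: one is filtered on attendance and the other is not. In a non-randomised study this adds a second source of selection to the one already acknowledged in section 3.2. Children who keep coming to a voluntary-time movement programme may be those whose motivation, health or family circumstances also make them more likely to progress over the half-year. If so, part of the measured advantage would appear even if the programme did nothing. The result would also answer a narrower question than the hypothesis and the scale-up decision pose, namely how regular attenders fare rather than how children in classes offered the programme fare.

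**Working it through.** **The plan's own figures (section 2.6).** Inputs: f = 0.15, two measurements, pre-post correlation 0.50, alpha 0.05/5 = 0.01, power at least 80%, two groups. For the within-between interaction, the noncentrality is λ = f² × N × m/(1 − r) = 0.0225 × N × 2/0.5 = 0.09N, with 1 and N − 2 degrees of freedom. The smallest N is 134 (power 0.803), as stated. With 25% dropout, 134/0.75 = 178.7, or 179, also as stated. The sample size is not in dispute.

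**The cut-off.** 11/14 = 78.6% and 10/14 = 71.4%, so the 75% threshold and the limit of three missed sessions agree. The 14 sessions include the pretest and posttest. Controls share only those two measurement occasions, so an eleven-session threshold has no meaning for them.

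**Bias when there is no true effect.** The document gives neither the share of children expected to miss more than three sessions nor any link between attendance and outcome. Both are therefore assumed. Let e be the share of the intervention arm excluded, ρ the correlation between attendance and a child's own change, and z_e the normal quantile for e. Removing the lowest attenders shifts the mean change of those retained by

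bias = ρ × φ(z_e)/(1 − e), in SDs of change.

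- e = 0.10, ρ = 0.2: 0.2 × 0.1755/0.90 = 0.039
- e = 0.25, ρ = 0.3: 0.3 × 0.3178/0.75 = 0.127
- ρ = 0: no bias at any e
- ρ = −0.2, e from 0.10 to 0.30: −0.04 to −0.10

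With r = 0.50 the SD of change is √(2 × (1 − 0.50)) = 1 raw SD, so these values are on the scale of d. Against the stated d = 0.30 they are 0.039/0.30 = 13% to 0.127/0.30 = 42%. One caution applies. In the formula that reproduces 134, λ = 0.09N equals δ²N/4 at a between-arm difference in change of δ = 0.60. Anyone reading the planned effect that way should halve these percentages.

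**Effect on the false-positive rate.** Take an assumed bias of 0.10 SD at n = 134 (67 per arm). The noncentrality is 0.10 × √(134/4) = 0.579. One-sided at 0.01, 1 − Φ(2.326 − 0.579) = 1 − Φ(1.747), about 4%. Under the undirected 0.01 F test that reproduces the sample size, the favourable tail is 1 − Φ(2.576 − 0.579), about 2.3% against a nominal 0.5%.

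**Simulation.** With 67 children per arm, 10-30% of the intervention arm excluded, ρ of 0.1-0.3 and 4,000 runs per setting, the bias is 0.02-0.15 SD. The one-sided error at nominal 0.01 is about 0.013-0.062.

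**Power.** Removing 10%, 20% or 30% of 67 intervention children and no controls lowers power at the planned effect from 0.80 to about 0.78, 0.74 or 0.70, unless the 25% dropout allowance is meant to cover these exclusions.

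**The case against.** The strongest reply is that the direction of bias is unproven. The test is of the time-group interaction, so stable differences between good and poor attenders that are present at both pretest and posttest cancel. Only a link between attendance and change matters, and the article reports none. Children with high initial motivation may even have less room to gain on a bounded scale, which would push the other way. This stands: a reader might infer that the rule necessarily inflates the effect, but the document supports only that it is likely to.

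Two other strong readings also fail. A reader might say that the rule, taken literally, deletes every control. The explanatory clause limits it to missed sessions of the PL intervention, which controls are never offered, so that reading is strained. (The clause also suggests that low attendance alone leads to exclusion, although joining (a) and (b) with a bare conjunction leaves this loose.) A reader might also compute the error rate at a one-sided 5% level, where a 0.10 SD bias gives about 14%. Section 2.6 plans 0.01, so about 4% is the relevant figure.

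It is fair to add that the rule is declared in advance, that the study is openly non-randomised, and that a fuller analysis plan might include an analysis of all children. The absence of such an analysis from the article is therefore not the point. The point is the exclusion that the article does fix, and nothing elsewhere in it offsets the one-sided selection.

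**Conclusion.** The concern holds. The main-study analysis selects on post-assignment attendance in the intervention arm and applies no counterpart in the control arm. That asymmetry follows directly from sections 2.1 and 2.7.2 and needs no assumption.

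Direction and size do need assumptions. If attendance is positively related to change, the interaction is likely to favour the intervention: by about 0.04-0.13 SD for 10-25% excluded and a correlation of 0.2-0.3, against a planned d of 0.30. Confidence is high on the asymmetry and moderate on the direction. The figures are illustrations, not estimates for this trial. Because the rule bears on the main effectiveness comparison, and through it on scale-up, it should be changed before analysis.

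**What to change.** In section 2.7.2, make the primary main-study analysis all eligible consented children with a baseline measurement, analysed in the condition of their class regardless of how many sessions they attended. The exclusion for a missing baseline can stay, as can the exclusion in section 2.2 of children with diagnosed special needs. Handle missing posttests with the EM imputation already planned. Report the at-least-11-of-14-sessions analysis only as a labelled per-protocol sensitivity analysis, with the number of children it removes.

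The cost is small but not nil. The effect estimate may be somewhat smaller. The posttest sits in session 14 (section 2.3.1), so some low attenders will have missed it and their values will be imputed rather than observed; the number imputed in each arm should be reported. The planned 134 (179 recruited) and power of 0.80 at the planned effect do not change.
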